#### Patient activation/empowerment

Patients will be asked to complete Patient Activation Measure (PAM) [21] at baseline, 12-weeks and 6-months. The PAM questionnaire collects data on an individual’s knowledge, skills and confidence to manage their health and is a global measure of an individual’s overall ability to manage their health.

Questionnaires will be given to patients in the clinic to take home and return by post in pre-paid envelopes alongside their accelerometer. We will look at return rates for questionnaires/accelerometers as part of the feasibility study and address issues/seek patient feedback on ways to improve this for the larger scale evaluation as necessary.

### Safety reporting

This is a small-scale feasibility study, and therefore a formal data monitoring committee will not be convened. We do not anticipate any major risks or adverse events to arise as a result of taking part in this study. If an adverse event does occur, it will be recorded and categorised in terms of relatedness and severity in line with the CTCAE criteria. The research team will meet bi-weekly to monitor interim safety/feasibility data by reviewing recruitment/adherence rates and adverse events. The NuTH NHS Trust will be informed according to trust policy.

### Data and statistical analysis

#### Quantitative analysis

The flow of participants throughout the trial will be reported in a Consolidated Standards of Reporting Trials (CONSORT) flowchart. Reasons for declining to take part in and for withdrawing from the study will also be recorded in the CONSORT flowchart. Descriptive statistics will be used to present baseline characteristics and feasibility outcomes. A paired t-test or Wilcoxon signed-rank test (depending on data distribution) will be used to evaluate changes in outcomes from pre- to post-intervention, with the mean difference and 95% confidence interval presented.

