## Aims and objectives

The aim of the study is to evaluate the feasibility and acceptability of VITALISE in the clinical setting within secondary care. This feasibility study will not include formal hypothesis testing because it is not powered to detect clinically meaningful changes in outcomes. The main aim is to gain insight into whether patients find VITALISE acceptable and whether it is feasible to deliver within routine clinical care.

In accordance with NIHR and CONSORT guidance for feasibility studies [16, 17], the primary objectives are to determine recruitment, retention and attrition rates, intervention uptake, engagement, adherence, and follow-up rates and to test the robustness of our data collection procedures. We will collect data on usability and individual patient views on VITALISE via semi-structured interviews to add important context to quantitative outcome data. Importantly, we will look at the demographics of patients who participate versus those who decline. We will seek information from those who decline to explore ways in which these barriers to participation can be overcome.

The secondary objective is to determine whether participation in the intervention leads to changes in outcomes including physical activity, diet, body weight, HbA1c, liver enzymes, liver stiffness, blood pressure, lipid profile (all measured as part of standard care using the NAFLD Care Bundle) [18] and patient activation/empowerment. These preliminary data will provide some indication of whether the intervention could be effective as part of routine clinical care.

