### Sample size

With reference to best practice guidelines on sample size requirements for feasibility studies [19] and practical time frames, we will aim to recruit 35 patients over a 6-month time period.

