#### Recruitment rate

Six patients recruited per month over a 6-month time period.

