#### Intervention uptake and engagement

 ≥ 80% of patients recruited logging in to the intervention.

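### Formal hypothesis testing is ruled out in the aims, yet significance tests are prescribed for the pre-to-post secondary outcomes, and a mean difference is reported even when the Wilcoxon test is chosen

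*Protocol article*

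**What the plan says.** Three parts of the protocol article bear on this point.

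- **Aims and objectives** takes a position on testing and gives a reason: "This feasibility study will not include formal hypothesis testing because it is not powered to detect clinically meaningful changes in outcomes". The same section sets the objective that the pre-to-post data serve: "The secondary objective is to determine whether participation in the intervention leads to changes in outcomes including physical activity, diet, body weight, HbA1c", followed by further outcomes. It calls the data preliminary.
- **Quantitative analysis** separates two groups of outcomes. For the first, "Descriptive statistics will be used to present baseline characteristics and feasibility outcomes". For the second, "A paired t-test or Wilcoxon signed-rank test (depending on data distribution) will be used to evaluate changes in outcomes from pre- to post-intervention". The same sentence goes on to fix the reported effect: "with the mean difference and 95% confidence interval presented". The mean difference and its interval are attached to whichever test is chosen. No other estimate is named for the Wilcoxon case, and the tests are not called exploratory.
- **Discussion** gives the purpose of the outcome data: to inform the likely size and variability of intervention effects, for the design of a larger evaluation.

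The sample size is not derived from a test: "we will aim to recruit 35 patients over a 6-month time period", with reference to feasibility guidance and practical time frames.

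**The concern.** There are two faults, one between sections and one inside a sentence.

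First, the aims exclude formal testing because the study lacks power for changes in outcomes, and the analysis section prescribes tests of those changes. An analyst must break one of the two statements. Whichever is followed, the report can be said to depart from the protocol.

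Second, the plan moves to the Wilcoxon test when the distribution makes a t-test look unsuitable, but keeps the mean difference as the reported effect. In that case the p-value and the estimate answer different questions. This can affect outcomes that are plausibly skewed, such as liver enzymes, triglycerides and liver stiffness. The protocol gives no distributions, so that list is an expectation and not a figure from the document.

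At stake is how the secondary results of a one-arm study are presented, and whether the estimates passed to a later trial are the right ones. The decision to progress is not at stake.

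**Working it through.** **1. Is there a real conflict?** The two statements, side by side:

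| Section | Position | Outcomes covered |
|---|---|---|
| Aims and objectives | No formal hypothesis testing, for lack of power | Changes in outcomes |
| Quantitative analysis | Paired t-test or Wilcoxon signed-rank test | Changes in outcomes, before to after |

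The outcomes are the same, and both named procedures are hypothesis tests. Nothing in the analysis sentence restricts them to some outcomes or withholds the p-values. The conflict stands on the text alone.

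**2. What do the tests reach?** The analysis section keeps the feasibility outcomes descriptive, and Table 3 lists these as the primary parameters. The progression criteria are counts and proportions: "Six patients recruited per month over a 6-month time period", at least "80% of patients recruited logging in to the intervention", and at least 70% of those accessing the intervention giving data at 6 months. None uses a test. The conflict is confined to the secondary pre-to-post outcomes.

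**3. Does the mean difference belong to the signed-rank test?** The estimate that corresponds to the signed-rank test is the Hodges-Lehmann pseudomedian, the median of all pairwise averages of the changes. It equals the mean when the changes are symmetric and generally differs when they are not. As an illustration, take a change distributed as exp(Z) − 1.25, with Z standard normal. This distribution is assumed and does not come from the protocol.

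- Mean: exp(0.5) − 1.25 = 1.649 − 1.25 = +0.40
- Median: exp(0) − 1.25 = −0.25
- Pseudomedian, by simulation: about −0.03

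The mean is clearly positive while the quantity that the test addresses is close to zero. The example shows that the targets differ. It does not show by how much they would differ in this study.

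**4. What would estimation alone deliver?** The protocol states no alpha, power, effect size or SD, so it has no power figure to reproduce. The half-width of a 95% t-interval for a mean change, in units of the SD of the change, is t(0.975, n − 1)/√n.

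| n | Where n comes from | Half-width |
|---|---|---|
| 35 | Planned sample, all followed up | 2.032/5.916 = 0.34 SD |
| 28 | 35 × 0.80 | 2.052/5.292 = 0.39 SD |
| 20 | 35 × 0.80 × 0.70 = 19.6 | 2.093/4.472 = 0.47 SD |

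The last two rows are floors set by the success thresholds and are not expected numbers. Intervals of this width serve the Discussion's purpose of showing size and variability, which does not require a p-value.

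**The case against.** The case for leaving the text alone has four parts.

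- **The framing is cautious.** The article speaks of preliminary data and preliminary changes, states no significance threshold and promises an estimate with an interval. A reader could take *formal* to leave room for informal tests. The cautious framing is real and lowers the severity. But the text never draws a formal/informal distinction, and the tests are prescribed without qualification.
- **Detail may sit in an analysis plan.** The rule for choosing between the tests, and the interval method, are commonly left to such a plan. That is fair, and the absence of a rule is not criticised here. An unseen plan cannot remove a conflict between two printed sentences, however, and any interval for the mean, t-based or not, is still an interval for the mean.
- **Deleting the tests is a preference.** Rewording the aims and labelling the tests exploratory would also settle the conflict. This stands, and the fix allows for it.
- **The harm is easily overstated.** A reader might infer that all outcomes are tested. They are not, because the primary ones stay descriptive.

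Two stronger readings also fail. One is that many uncorrected tests make a false positive likely: 21 independent tests at 5% would give 1 − 0.95^21 = 66%, and the nine domains in the secondary objective 1 − 0.95^9 = 37%. The 5% level, the independence and the count of 21 are all assumptions. Related measures, such as weight with waist or the activity bands cut from one accelerometer trace, break independence. Nor would reporting 95% intervals lower the figure, since for a t-test an interval that excludes zero is the same event as p < 0.05. The other is that test and interval would often contradict each other. In simulations with n = 20, the two verdicts disagreed in about 8–11% of runs for shifted log-normal data. They also disagreed in about 3–6% for normal changes with a true shift, and in 2% for the log-normal data with no shift. About half of the first rate is therefore ordinary borderline disagreement, and its settings are not in the protocol.

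**Conclusion.** The point holds, as a should-fix limited to the secondary pre-to-post outcomes. The aims and the analysis section contradict each other on whether these outcomes are tested, and the mean difference is the wrong companion to a Wilcoxon test. The contradiction rests on the text and needs no assumption. The mismatch of estimate and test matters only where the Wilcoxon test is chosen and the changes are asymmetric; no rate can be given for this study. Neither the multiplicity figures nor the simulated disagreement rates are evidence of harm here. The primary feasibility outcomes, the progression criteria and the sample size are unaffected.

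**What to change.** Replace the test sentence in the Quantitative analysis section with wording such as:

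> Changes from baseline to 6 months will be described by the mean change with 95% CI; no significance tests or p-values will be reported, and the intervals are not evidence of efficacy. For outcomes named in advance as skewed (such as liver enzymes, triglycerides and liver stiffness), the ratio of geometric means with its 95% CI will be reported.

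The ratio needs strictly positive values, so the advance list should contain only such outcomes.

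If the sponsor keeps the tests, three changes are needed together: reword the statement in Aims and objectives, label the tests exploratory, and report the Hodges-Lehmann estimate with its own interval wherever the Wilcoxon test is used.

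The first option rewrites one paragraph, needs no extra data and brings the analysis into line with the stated aims. Its only downside is that p-values cannot be quoted.

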## Methods

### Study design

This feasibility study will use a single-centre (Newcastle upon Tyne Hospitals NHS Foundation Trust (NuTH)), one-arm, prospective design. Feasibility and acceptability of recruitment, the intervention (VITALISE), and associated outcome measures will be assessed using a mixed-methods approach. Health-related outcomes will be quantitatively assessed at baseline and 6-months. An interim measure of self-reported weight, physical activity and self-efficacy (via the Patient Activation Measure (PAM)) will be recorded at 12-weeks.

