#### Completion and follow-up rate

 ≥ 70% of those accessing the intervention providing data at 6-months follow-up.

These criteria aim to retain a sufficient sample size to determine acceptability and feasibility.

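### The only stated analysis of outcome change is a two-point paired test, which describes patients with a 6-month value and may overstate benefit if those lost did worse

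*Protocol article*

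**What the plan says.** **Analysis.** Under Quantitative analysis, the protocol article gives one method for outcome change. It is a paired t-test, or the Wilcoxon alternative where the distribution calls for it, and the article says of it: "will be used to evaluate changes in outcomes from pre- to post-intervention, with the mean difference and 95% confidence interval presented". It names no analysis population there.

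**Tolerated loss.** The planned size is given as "we will aim to recruit 35 patients over a 6-month time period". The criteria for progressing accept at least "80% of patients recruited logging in to the intervention" (Intervention uptake and engagement) and at least "70% of those accessing the intervention providing data at 6-months follow-up" (Completion and follow-up rate). The second percentage is taken over users only, so recruits who never log in are outside its denominator.

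**Data at 12 weeks.** Study design says: "An interim measure of self-reported weight, physical activity and self-efficacy (via the Patient Activation Measure (PAM)) will be recorded at 12-weeks". The sections on physical activity and patient activation confirm that the Godin score and PAM are taken at baseline, 12 weeks and 6 months.

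**Source of the 6-month values.** Weight, waist and hip circumference, blood pressure, bloods, Fibroscan and the clinical scores come from standard care (Preparation procedures, Table 1, Secondary outcome measures). Questionnaires and accelerometers are research measures returned by post.

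**Use.** Aims and objectives treats the changes as a preliminary pointer to effectiveness in routine care. The Discussion expects them to show how large and how variable effects may be, and to feed the design of a larger evaluation.

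**The concern.** A pre-post difference can be formed only for a patient who has both values. Unless missing values are filled in, the reported mean and interval therefore describe the patients who were followed up, not everyone recruited. In a weight-loss programme it is plausible that patients who stop engaging lose less weight and are also less often measured. The article itself collects log-in, module and coaching data because it expects change to depend on engagement. If both links hold, the observed mean leans towards benefit, and its confidence interval, which reflects sampling error only, does not show this. What is at stake is a secondary result, but one the article means to carry into the design of the next study. The 12-week PAM and Godin scores, which could inform on patients lost later, have no role in a two-point test.

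**Working it through.** **Inputs from the article:** 35 recruits; at least 80% log in; at least 70% of those accessing give 6-month data.

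**Consistency of the sample size.** The recruitment criterion, "Six patients recruited per month over a 6-month time period", gives 6 × 6 = 36, in line with 35. No power or precision inputs are given, so there is no further figure to reproduce.

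**How many may lack a 6-month value with both criteria met**

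- Minimum log-ins: 0.80 × 35 = 28, leaving 7 non-users.
- Minimum users with 6-month data: 0.70 × 28 = 19.6, rounded up to 20.
- All 7 non-users have standard-care values: 28 − 20 = 8 missing, 8/35 = 23%.
- No non-user gives data: 35 − 20 = 15 missing, 15/35 = 43%.
- All 35 log in: 0.70 × 35 = 24.5, rounded up to 25; 35 − 25 = 10 missing, 10/35 = 29%.
- With 36 recruits the worst case is 29 log-ins, 21 followed up and 15 missing (42%).

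The 43% case is more plausible for the postal questionnaires and accelerometers than for the clinic measures.

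**Precision.** The 95% half-width in SDs of change is t(0.975, n−1)/√n: 0.34 at n = 35 and 0.47 at n = 20.

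**Possible bias.** Let m be the mean change in those without data, as a fraction of the mean change in those with data (an assumption; the documents give no value). In the worst case, the ratio of observed mean to all-recruit mean is 35/(20 + 15m):

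| m | ratio |
|---|---|
| 0 | 35/20 = 1.75 |
| 0.25 | 35/23.75 = 1.47 |
| 0.5 | 35/27.5 = 1.27 |
| 1 | 35/35 = 1.00 |
| 1.25 | 35/38.75 = 0.90 |

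With m = 0 and fewer missing, the ratio is 35/25 = 1.40 (10 missing) or 35/27 = 1.30 (8 missing).

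**Illustration in kg.** Assume a true mean change of −2 kg, an SD of 5 kg, and retention correlated 0.3 to 0.5 with better weight change. The expected observed mean is then −3.0 to −3.7 kg with 20 of 35 retained, and −2.7 to −3.2 kg with 25 of 35. All these inputs are assumed. With zero correlation the bias vanishes, and with a negative one it reverses.

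**The case against.** The strongest reply is that this is mostly silence in a condensed article. Analysis sets and missing-data handling are commonly left to an analysis plan, which is not shown, and a paired test can be run on filled-in values. That stands as far as it goes: the absence of a missing-data section is not the point here. The point is that the one method the article does state, run in the ordinary way, answers a narrower question than the use made of it, and better analyses of data already collected are available.

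Three stronger readings are tempting, and the documents do not support them.

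- *The result overstates benefit.* Neither the direction nor the size of any bias follows from the documents; over the range tried, the ratio runs from 0.90 to 1.75.
- *Fifteen of 35 will go unscored.* That is a worst case at the exact thresholds. Nothing says non-users give no 6-month data, the clinic measures are standard care, and the thresholds are floors, not expected rates.
- *The larger study will be sized on too large a change.* The article says only that the data will inform its design, if one is appropriate.

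It is also fair that the changes are secondary, that formal hypothesis testing is disclaimed, and that attrition will be visible through the CONSORT flowchart, recorded reasons for loss, interviews with those who drop out, and questionnaire and accelerometer return rates. These show who is missing. They do not alter the estimate or its interval.

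**Conclusion.** The point holds in a limited form. The stated paired analysis describes change among patients with a 6-month value. The progression criteria can be met with 8 to 15 of 35 recruits (23% to 43%) lacking one in the scenarios worked through, the upper end requiring that no non-user gives data. In that worst case the observed mean would be 1.75 times the all-recruit mean if the missing patients had no change, and unbiased if they changed equally. Which applies is an assumption the documents cannot settle, so the supportable statement is that benefit may be overstated. The group should also be called patients followed up, not completers, because giving 6-month data and completing the intervention are different things. Since the results are secondary and meant to inform a later design, this is a worthwhile, inexpensive improvement and not a flaw that undermines the feasibility aims.

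**What to change.** Keep the paired summary and add to it:

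1. Label it as change among those followed up, and give n for each outcome.
2. For PAM and Godin, fit a repeated-measures mixed model to the baseline, 12-week and 6-month scores of all recruits. This assumes that missingness depends only on observed values, which should be stated.
3. For weight and the clinic measures, add an estimate that assigns no change to patients without a 6-month value. Present it as a sensitivity analysis, not as the main result, because it is itself an untestable assumption.
4. Tabulate baseline characteristics of patients with and without 6-month data.
5. Carry the resulting range, not only the observed-pairs mean, into the design of the larger evaluation.

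The cost is a few extra analyses of data already collected, and probably a smaller headline change. No extra patients or visits are needed.

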#### Qualitative analysis

Interviews will be audio recorded, transcribed verbatim, and analysed using thematic analysis [25]. All transcripts will be coded independently by one member of the research team, with a proportion (~ 50%) independently coded by a second research team member. Codes and potential themes will be discussed and agreed at the research team level and agreed for reporting purposes.

### Research ethics approval

An independent NHS Research Ethics Committee (North East—Tyne & Wear South Research Ethics Committee) has provided a favourable ethical opinion for this study to commence (IRAS ID: 313,662).

### Patient and public involvement

We have consulted extensively with patients with NAFLD to identify their supported self-management needs and preferences. A consistent finding is their lack of knowledge about what NAFLD is, how it progresses (and that it can progress) and current management options (“*the only thing they said was to try and sort of lose a bit of weight…apart from that I’ve never ever had any advice or anything else”*). Most patients we consulted did not understand the links between their lifestyle behaviours and NAFLD, including its progression. A lack of knowledge that NAFLD can be managed by making lifestyle changes was evident. This is likely due to the lack of NAFLD-specific resources available to facilitate communication with patients (“*I couldn’t really go into it. It was so brief, what I got off my GP. She did tell me I could Google it and read up about it…But I haven’t*”).

The findings from a series of interviews and workshops with patients have led to the development of VITALISE. The involvement of specifically trained lifestyle coaches was considered an essential intervention component to promote ongoing engagement and help patients overcome barriers to achieving clinically and personally meaningful goals.

Patients who assessed usability of VITALISE reported feeling empowered, informed and motivated to make lifestyle changes.

